#### **Research Follow-Up Procedures – THIS IS PART 2 OF THE RESEARCH PROVISIONS**

We will assess outcome measures monthly for patients assigned to the THRIVE+ intervention arm, in order to satisfy a requirement of our funder. We will assess all outcome measures for all study participants at 6 months post-enrollment in the clinical program – again, to satisfy a requirement of our funder – and at 12 months post-enrollment in the clinical program.

As part of the research provisions, pharmacy liaisons-patient navigators will systematically screen patients assigned to the intervention arm with the THRIVE screener every three months to assess for new or unmet HRSN. These re-screens will take place during the monthly follow-up touches that are part of the existing clinical program.

We will analyze data collected via routine clinical care to ascertain primary and secondary study outcomes. There are three data sources for data collected as part of routine care:

1. BMC Clinical Data Warehouse
2. BMC HealthNet Claims Data
3. Pharmacy Care Program client tracking system

In addition, we will analyze data collected for research purposes. There is one data source for data collected for research purposes outside of routine clinical care:

1. Connection to resources at Action for Boston Community Development (ABCD), Inc.

To assess receipt of services our community partner for this study, ABCD, will check how many of the intervention arm study participants used services at ABCD to help address HRSN. ABCD will provide BMC with data to confirm patient receipt of services, the type of service received, and the date of receipt.

A Pharmacy Liaison-Patient Navigation Intervention to Reduce Inpatient and Emergency Department Utilization among Primary Care Patients in a Medicaid Accountable Care Organization: A Pragmatic Trial  
Version 1.3, August 5, 2021

611 Table 1. Study Outcomes

| Outcome measure                                                                    | Data Source                                                       | Data collected as part of Routine Care or for Research? | Measurement Time Points (Post-Enrollment)                                                                                                                                              |

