| Patients to receive services to meet their HRSN     | Action for Boston Community Development data                                                                                                       | Research     | Quarterly – All enrolled patients                                                                                                                                                      |
| Connection to housing resources                     | Action for Boston Community Development data                                                                                                       | Research     | Quarterly – All enrolled patients                                                                                                                                                      |
| Connection to employment resources                  | Action for Boston Community Development data                                                                                                       | Research     | Quarterly – All enrolled patients                                                                                                                                                      |
| Connection to food                                  | Action for Boston Community Development data                                                                                                       | Research     | Quarterly – All enrolled patients                                                                                                                                                      |
| Patient-level average of Proportion of Days Covered | BMC HealthNet Plan claims data                                                                                                                     | Routine Care | Quarterly – All enrolled patients                                                                                                                                                      |

|                                        |  |  |  |
|----------------------------------------|--|--|--|
| (PDC) for pharmaceutical prescriptions |  |  |  |
|----------------------------------------|--|--|--|

Table 2. Post-Hoc Measures

| Post-hoc measure                                     | Data Source                 | Data collected as part of Routine Care or for Research? | Measurement Time Points (Post-Enrollment) |

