|  | 
categorical variables. Due to a potential high number of patients with zero-count visits (136 out of 364, 37%), we employ a zero-inflated negative binomial model, which is a two-part model that examines simultaneously the odds of any visit, and the rates of visits among those patients who have any health care utilization. We use Bayesian Information Criteria as the model goodness-of-fit measure to compare zero-inflated negative binomial model with other models for the rates outcomes, including over-dispersed Poisson model, and negative binomial model. As a sensitivity analysis, we also model only the binary outcome of any utilization using logit link function. In the adjusted regression models, we will control for any factors including baseline utilization that are found statistically significant between the two arms. We report odds ratios and 95% CI for binary outcome (e.g., any visit) and rate ratios for the outcomes of inpatient and ED visits. We also compare the secondary outcomes of health-related social needs (e.g., connected to community-based partner; received services through referral to community partner; referrals and visits to hospital food pantry; received utility shutoff protection letter) between the two arms and examine adjusted intervention effect using logistic regression with odds ratio and 95% CI.
 
The primary analyses will be based on intent-to-treat. Because participants may receive varying “doses” of the intervention, we will also analyze the intervention effect according to whether participants received a minimum dose of the intervention. If the pharmacy liaison-patient navigator documents in their first telephone assessment that the patient has received the THRIVE screening in the past three months, and rescreens the patient if they have not been screened in the past three months, we consider the patient to have received the minimum intervention dose.
 |

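### Protocol and SAP disagree on whether control patients are looked up at the community partner, so the between-arm test of partner outcomes may not be interpretable

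*Combined protocol and SAP*

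**What the plan says.** Protocol section 9 (Research Follow-Up Procedures) names ABCD as the one data source collected for research rather than routine care. It then says that ABCD "will check how many of the intervention arm study participants used services at ABCD to help address HRSN" and will return confirmation, type and date of service. No other text describes how partner data are obtained.

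Two other places in section 9 point the other way. A general sentence reads "We will assess all outcome measures for all study participants at 6 months post-enrollment in the clinical program", and the same sentence repeats this for 12 months. Table 1 gives "Action for Boston Community Development data" as the source for services received and for connection to housing, employment and food, each timed "Quarterly – All enrolled patients".

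The SAP synopsis (Statistical method) lists "connected to community-based partner; received services through referral to community partner" among outcomes to be compared "between the two arms and examine adjusted intervention effect using logistic regression with odds ratio and 95% CI". The same list includes "referrals and visits to hospital food pantry; received utility shutoff protection letter"; protocol Table 2 takes social-needs referrals and services of that kind from the hospital data warehouse for all participants.

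SAP section 4.3 (missing data) covers utilization data in the warehouse and claims. It says nothing about partner data or about a control patient who was never checked.

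**The concern.** A between-arm odds ratio needs the outcome to be ascertained in the same way in both arms. The only described look-up at the partner covers one arm. Not having been checked is not the same as not having used the service. Under protocol section 8, control patients receive printed guides to community resources and may see a clinic-based navigator who uses the THRIVE directory, so some control use of community organizations is plausible.

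What is at stake is the first link in the hypothesis of protocol section 12.1: that THRIVE+ raises connection to and receipt of resources, and thereby lowers acute use. An odds ratio for partner connection would be read as evidence for that link. With one-arm ascertainment it would not be such evidence, whatever its size.

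**Working it through.** The documents give no expected rate, power or sample size for partner connection, so there is no planned figure to reproduce. The only documentary input is the arm size, 182 per arm (protocol section 12.2). The use rates below, 1% to 10%, are assumptions. The SAP does not give a source for its partner outcomes; I take the partner to be ABCD, as protocol section 9 does.

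**Step 1. What happens to an unchecked control.** No rule is stated, so there are two cases.

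- *Left missing.* The outcome exists in THRIVE+ only, and no between-arm effect can be estimated.
- *Coded as non-use.* The control cell is 0/182. With users and non-users in THRIVE+ and only non-users in control, the treatment term in the logistic model is quasi-completely separated. The maximum-likelihood odds ratio is infinite and the usual 95% CI has no meaning.

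**Step 2. How few THRIVE+ users would look significant in the second case.** With r users against 0 at 182 per arm, the two-sided Fisher p-value is 2 × C(182, r) / C(364, r).

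- r = 5: p = 0.061
- r = 6 (6/182 = 3.3%): p = 0.030

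The uncorrected chi-square statistic is 364r / (364 − r).

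- r = 3: 1092/361 = 3.02, p = 0.082
- r = 4 (4/182 = 2.2%): 1456/360 = 4.04, p = 0.044

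The SAP does not name Fisher's test for these outcomes. I use it because it stays defined with an empty cell and is the more cautious of the two.

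**Step 3. False significance when true use is equal in both arms.** With controls coded as non-users, Fisher's test rejects when X ≥ 6, where X is binomial with n = 182 and probability p. The last column is the Fisher rejection rate when both arms are looked up and use is p in each.

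| Assumed true use, both arms | Expected THRIVE+ users (182p) | Rejects, controls coded non-user | Rejects, both arms looked up |
|---|---|---|---|
| 1% | 1.8 | 1.1% | 0.4% |
| 2% | 3.6 | 16.0% | 1.5% |
| 3% | 5.5 | 46.5% | 2.1% |
| 5% | 9.1 | 89.6% | 2.7% |
| 10% | 18.2 | over 99.9% | 3.2% |

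Every false rejection in the third column favours THRIVE+. By uncorrected chi-square (X ≥ 4) the corresponding rates are 11.1%, 49.5%, 79.8%, 98.2% and over 99.9%.

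**The case against.** The strongest reply is that the intervention-arm sentence is a drafting slip. Table 1 and the general sentence in section 9 say that everyone is assessed. The waiver justification in section 13 speaks of following all subjects to assess access to services for social needs, in both arms. The schedule of events puts the ABCD row under the quarterly column, not the monthly column reserved for the intervention arm; this is weaker support, because the THRIVE+ screener sits under the same column. The reply stands to this extent: a reader might infer that partner data are collected for THRIVE+ only, and the documents do not establish that. They contradict each other. But the only procedure actually described is one-armed, so the reply does not remove the problem.

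A reader might also infer that the control count is zero by construction and that any effect is manufactured. Neither follows. Zero requires a coding step that no text states. And section 8 gives THRIVE+ a dedicated ABCD staff member, a contact that did not exist before the study, so part of any difference may be real. The documents do not let the two parts be separated.

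Scope is limited too. The protocol classes these outcomes as intermediate, and the SAP's formal lists of secondary outcomes (synopsis and section 6.1) do not name the partner. The comparison is nevertheless written into the SAP's statistical method.

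Finally, a reader might extend the point to identified social needs, because THRIVE+ patients are re-screened every three months. Table 1 sources that measure from THRIVE-Basic screening results for all enrolled patients, and identifying more needs is a stated objective of THRIVE+. I do not extend it.

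**Conclusion.** The point holds as an unresolved contradiction with a definite consequence. If the look-up in section 9 is carried out as described, the SAP's between-arm comparison of partner outcomes is either inestimable or biased toward THRIVE+ with no finite odds ratio.

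The size of the bias depends on true partner use, which the documents do not give, and on unchecked controls being coded as non-users. It is negligible at 1% use (1.1% false significance by Fisher's test) and dominant at 5% (89.6%, against 2.7% with equal look-up). If both arms were in fact looked up in the same way, this bias is absent and only the text needs correcting.

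The primary composite, the other utilization outcomes, and the food-pantry and utility-letter outcomes are not affected.

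**What to change.** Reconcile protocol section 9, Table 1 and the SAP synopsis, and state which arms the partner matched. Then take one of two routes.

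1. **Look up both arms.** The partner matches both arms' lists with the same matching rule and time window. Section 9 is amended to refer to all study participants, and the SAP says how a non-match is coded. First confirm that the waiver and data-use terms allow control identifiers to go to the partner: section 13 argues for waivers in both arms but does not describe that disclosure. Cost: a longer matching list and possibly a data-use addendum. SAP section 3.2 has recruitment ending in March 2020, so a new look-up would be retrospective. Even then, receipt of services through referral to the partner may largely reflect a route provided in THRIVE+ only, and should be described as close to a measure of delivery.
2. **Drop the comparison.** Remove the between-arm tests of partner-based outcomes from the SAP, restrict the four ABCD rows of Table 1 to THRIVE+, and report the THRIVE+ proportion as descriptive process data. Cost: wording only.

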The pharmacy liaison-patient navigators will partner with a community organization, Action for Boston Community Development (ABCD). A dedicated ABCD staff member will help connect participants receiving THRIVE+ to ABCD community-based programs, services, and resources at ABCD's decentralized neighborhood sites and centralized departments. Resources include assistance with childcare, employment, utilities, and housing. The pharmacy liaison-patient navigators will initially assess patient needs, formulate recommendations for resources to address HRSN, and interface directly with the dedicated ABCD staff member to coordinate receipt of resources for their patients. Although BMC has a longstanding relationship with ABCD, prior to THRIVE+ there was no designated individual at ABCD to help connect BMC participants to its services, either directly or through their network of affiliations. One 0.5 FTE ABCD employee will be supported to help connect the THRIVE+ participants to services. After the initial 30-45-day intervention period, the pharmacy liaison-patient navigators will contact

participants monthly, re-administering the THRIVE screener every three months to assess for new or unmet HRSN needs until 1 year following enrollment in the clinical program.

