### **4.2 Participants' characteristics at inclusion**

Table 1 shows descriptive characteristics for the usual care and enhanced usual care groups. The usual care and enhanced usual care groups differed in the respective proportion who spoke English (78% vs. 87%), reported housing insecurity (9% vs. 13%), received a referral to the hospital food pantry in the past 12 months (14% vs. 25%), had at least one visit to hospital food pantry in past 12 months (12% vs. 20%) and had a diagnosis of PTSD (21% vs. 14%). The majority belonged to a racial/ethnic minority group, and 96% had received screening for health-related social needs in the past year. Approximately two-thirds of patients had significant medical comorbidity, and nearly half carried a diagnosis of depression.

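### Connection to the community partner (ABCD) has no baseline look-back and no new-use rule, so continuing use by existing ABCD clients can count as a connection, and prior use is not a planned covariate

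*Combined protocol and SAP*

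**What the plan says.** **Ascertainment.** Protocol section 9 (Research Follow-Up Procedures) says that ABCD "will check how many of the intervention arm study participants used services at ABCD to help address HRSN", and that "ABCD will provide BMC with data to confirm patient receipt of services, the type of service received, and the date of receipt".

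**Outcomes and timing.** Table 1 lists four outcomes sourced from ABCD: receipt of services, "Connection to housing resources", and the matching employment and food items. They are classed as intermediate. The time-point column is headed as post-enrolment, and each of these rows reads "Quarterly – All enrolled patients". In the schedule of events (Attachment 1), the ABCD row is marked under the quarterly column only.

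**Analysis.** The Statistical method entry of the SAP synopsis compares two ABCD items between arms by adjusted logistic regression: "connected to community-based partner; received services through referral to community partner". Adjustment is for factors found to differ significantly between the arms. Prior ABCD use is not among the variables listed in protocol section 12.3 or under Measures in the SAP synopsis.

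**Prior contact.** Section 8 begins one sentence with "Although BMC has a longstanding relationship with ABCD" and goes on to say that no dedicated ABCD contact for the hospital's patients existed before THRIVE+.

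**Comparable resource.** SAP section 4.2 does report use of the hospital food pantry in the 12 months before inclusion (usual care vs THRIVE+): referral 14% vs 25%, at least one visit 12% vs 20%.

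**The concern.** Connection suggests a link that navigation brought about. The only operational rule is whether the patient used ABCD services. Without a look-back, a patient receiving help from ABCD before enrolment who receives it again afterwards looks the same as one whom the navigator brought in.

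Two consequences follow. If existing clients are equally common in the two arms, they add the same background to both and dilute a real effect. If they are commoner in one arm, they shift the comparison in that arm's favour. The SAP's covariate rule cannot respond to such a difference, because it acts only on variables that have been collected.

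These outcomes test the first link in the hypothesis of protocol section 12.1: that THRIVE+ raises connection to and receipt of resources, and through that lowers acute utilization. A blurred measure of that link makes the main result harder to interpret, whichever way it falls.

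**Working it through.** The plan states no sample size, power or expected rate for these outcomes, so there is no figure to reproduce. The calculations below illustrate size only.

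**1. Was prior resource use balanced where it was measured?** SAP 4.2 percentages, applied to an assumed 182 per arm and rounded to counts:
- Pantry referral: 25/182 vs 46/182. OR = (46/136)/(25/157) = 2.12; Pearson chi-square p = 0.005.
- Pantry visit: 22/182 vs 36/182. OR = (36/146)/(22/160) = 1.79; p = 0.045 (0.063 with continuity correction).

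Both were higher in THRIVE+.

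**2. Dilution of a real effect.** Assumptions, none from the documents except 182 per arm:
- Both arms are looked up.
- Prior use p is 10–20% in each arm, a range guided by the pantry visit figures.
- A fraction c of prior users continues after enrolment.
- Everyone else makes a new connection with probability q: 5% in usual care, 12% in THRIVE+.

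Counted rate = pc + (1 − pc)q. Power uses the two-proportion normal approximation, two-sided 0.05: Φ[(|d| − 1.96·se0)/se1], where d is the difference in rates, se0 its pooled and se1 its unpooled standard error.

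With existing clients excluded: 5% vs 12%, OR = (0.12/0.88)/(0.05/0.95) = 2.59, power 67%.

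Example, p = 0.10 and c = 1: usual care 0.10 + 0.90 × 0.05 = 0.145; THRIVE+ 0.10 + 0.90 × 0.12 = 0.208; OR = (0.208/0.792)/(0.145/0.855) = 1.55.

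| Prior use | Continuing | Counted rates | OR | Power |
|---|---|---|---|---|
| 10% | all | 14.5% vs 20.8% | 1.55 | 35% |
| 20% | all | 24.0% vs 29.6% | 1.33 | 23% |
| 10% | half | 9.8% vs 16.4% | 1.82 | 47% |
| 20% | half | 14.5% vs 20.8% | 1.55 | 35% |

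If prior users who stop are given no chance of a new connection, the half-continuing rows become OR 1.79 and 1.50.

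**3. No true effect, unequal prior use.** Prior use is set at 12% vs 20%, copying the pantry visit figures, with new connection 5% in both arms:
- All continue: 0.12 + 0.88 × 0.05 = 16.4%; 0.20 + 0.80 × 0.05 = 24.0%; OR 1.61; significant in about 44% of trials.
- Half continue: 0.06 + 0.94 × 0.05 = 10.7%; 0.10 + 0.90 × 0.05 = 14.5%; OR 1.41; about 19%.
- A quarter continue: 7.9% vs 9.8%; OR 1.27; about 9%.

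If new connection is 20% in both arms and all prior users continue, the OR is 1.34 and about 25% are significant. These percentages are conditional on that imbalance being present.

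**4. If only THRIVE+ patients are looked up.** No between-arm odds ratio can then be formed. At 10–20% prior use with all continuing, 0.10 × 182 to 0.20 × 182, or about 18 to 36 existing clients, would be credited to THRIVE+.

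**The case against.** Several stronger readings are tempting, and the documents do not support them.

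- **That services received only before enrolment are counted.** They need not be. ABCD supplies dates and Table 1 is headed as post-enrolment, so such services can be excluded. What remains is continuing use by existing clients.
- **That prior use cannot be adjusted for.** The documents show only that adjustment is not planned and no baseline extract is scheduled. ABCD supplies dated records, so an earlier window may be obtainable.
- **That the false-positive rate is 44%.** That figure takes a 12% vs 20% difference as fixed. If assignment by record-number parity balances prior use in expectation, the unadjusted test keeps its nominal size. A systematic difference would need selective enrolment. Section 9 leaves room for that, because arm-specific staff approach patients without a script, but nothing shows that it occurred for ABCD use.

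Other counter-arguments carry weight. One of the two SAP items is tied to referral, which partly limits attribution. However, the ABCD fields listed in section 9 include no referral source, and the other item, connection to the partner, has no such limit. An institutional relationship is not evidence that these patients used ABCD, and the food pantry is a different kind of service, so the assumed 10–20% is a guess. The outcomes are intermediate in the protocol, and SAP 6.1 does not list ABCD among the secondary outcomes. Finally, the hypothesis speaks of connection and receipt, not first-ever use: counting only new service types would discard genuine re-connection by a navigator.

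None of this supplies a definition of connection or a baseline measure.

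**Conclusion.** The point holds in a limited form. The ABCD outcomes have no baseline look-back and no new-use rule, so continuing use by existing clients can be scored as a connection, and prior ABCD use is not a planned covariate. For the pantry, by contrast, the SAP reports 12-month prior use, and the arms differed.

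The true size cannot be known from the documents. On the assumptions above, an odds ratio of 2.6 would shrink to somewhere between 1.33 and 1.82, depending on prior use and on whether all or half of prior users continue. A pantry-like imbalance with no true effect and 5% new connection would give about 1.4–1.6. Both ranges shrink if fewer patients continue, and both require a control-arm look-up, which section 9 does not describe.

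This is an inexpensive improvement to a test of mechanism. It does not affect the primary outcome.

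**What to change.** 1. In section 9, Table 1 and the schedule of events, extend the dated ABCD extract to the 12 months before enrolment as well as the 12 months after. Report prior ABCD use by arm with the baseline characteristics.
2. In the SAP, define the ABCD items and enter prior ABCD use (yes/no) in the logistic model whatever its significance.
3. Report two measures side by side: new connection (a service type received after enrolment and not in the prior 12 months) and any use after enrolment. The new-type measure should not be the sole definition, so that re-connection is not lost.
4. Reconcile section 9, which limits the ABCD check to the intervention arm, with Table 1, which says all enrolled patients. The between-arm analysis in the SAP synopsis, and any adjustment for prior use, requires the look-up in both arms.

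**Cost.** Wording changes and a wider date range in a look-up that ABCD already performs, plus a control-arm look-up if one is not already intended. The data request and the HIPAA waiver text must cover the look-back, because section 13 justifies the waiver by prospective follow-up to 12 months after enrolment. The new-connection measure will have fewer events than any use.
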